3	Alternative composite threshold: ≥100 m absolute MWD gain	Tests sensitivity to an absolute rather than relative distance criterion
4	Functional improvement component only (no revascularization criterion)	Isolates the predictive relationship with functional adaptation. Mandatory pre-specified secondary analysis; reported in all primary publications regardless of composite outcome result.
5	Revascularisation-free survival component only	Isolates the predictive relationship with intervention requirement. Mandatory pre-specified secondary analysis; reported in all primary publications regardless of composite outcome result.
6	Restriction to guideline-concordant revascularisation events only	Removes patient-preference-driven events to reduce confounding; specifically examines discordant cases (functional improvement achieved but revascularisation occurred)
7a	Four-predictor model: muscle density, VAT, age, sex (excluding baseline MWD)	Robustness check with an EPV approximately 10; tests stability of primary model estimates when baseline MWD is excluded
7b	Three-predictor model (muscle density, VAT, age; excluding sex)	Robustness check with an EPV approximately 13–14
8	Alternative muscle density threshold: 33 HU	Tests lower threshold sensitivity for myosteatosis classification (Martin et al. [21] value for BMI ≥ 25 kg/m^2^); see also Section 2.6
9	Alternative muscle density threshold: 41 HU [Martin et al. [21], BMI < 25 kg/m^2^ stratum]	Tests higher threshold sensitivity for myosteatosis classification; see Section 2.6
10	Alternative VAT threshold: --20 cm^2^ (110 cm^2^ M; 80 cm^2^ F)**†**	Tests sensitivity to a more conservative VAT threshold
11	Alternative VAT threshold: +20 cm^2^ (150 cm^2^ M; 120 cm^2^ F)**†**	Tests sensitivity to a more stringent VAT threshold
12	Adherent subgroup (≥30/36 sessions completed)	Per-protocol analysis to assess treatment-specific effects
13	30% treatment failure rate scenario (approximately 30 failures)	Reports model performance and power under a more optimistic clinical assumption
14	Expanded confounding model: primary five predictors plus ABI, smoking status, diabetes, Clinical Frailty Scale score, TASC II classification, SMI, SAT	Pre-specified secondary expanded model; EPV approximately 3–4 (acknowledged limitation); designated as robustness sensitivity analysis; tests whether primary predictor associations are independent of additional clinical confounders

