### Secondary and exploratory outcomes

Secondary outcomes, evaluated at baseline (T0) and three months (T1), include: standardized treadmill MWD and PFWD; absolute and relative change in MWD from baseline to T1 (continuous secondary outcomes); 30-second chair stand test repetitions; bilateral handgrip dynamometry (kg); 2-minute walk test distance; and Walking Impairment Questionnaire (WIQ) domain scores. Exploratory outcomes assessed at 6, 12, and 18 months—such as late revascularization, MALE, MACE, and all-cause mortality—are obtained through structured telephone follow-up, medical records review, and registry linkage. Given the anticipated low event counts during extended follow-up in this cohort, exploratory outcomes will be reported descriptively and interpreted as hypothesis-generating only.

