Classification thresholds for the primary predictors (skeletal muscle density for H1; VAT area for H2) will be derived prospectively within this cohort and treated as pre-specified study outcomes rather than assumptions. For the binary primary composite outcome, optimal cut-points will be identified by maximizing the Youden index (J = sensitivity + specificity -- 1) using the cutpointr R package; 95% confidence intervals will be obtained via 1000-sample bootstrap resampling. Separate derivations will be conducted for skeletal muscle density (single threshold) and VAT area (sex-stratified: men and women analyzed independently to account for dimorphic adipose tissue distribution). For the secondary time-to-revascularization outcome, optimal cut-points will also be identified by maximizing the log-rank statistic via survminer::surv_cutpoint(), providing a time-to-event-appropriate complement to the Youden-index approach. Each threshold derivation will report the optimal cut-point value, Youden index, sensitivity, specificity, and 95% bootstrap CI. As thresholds will be derived from the same cohort used for evaluation, internal optimism is anticipated and explicitly acknowledged. Thus, all threshold-based classification results will be interpreted within the derivation-cohort framework, with external validation in an independent PAD multicenter cohort as the pre-specified mandatory next step prior to clinical translation. Literature-derived thresholds from non-PAD populations will be retained as pre-specified sensitivity analyses (Table 3) to facilitate transparent cross-referencing with existing oncological and metabolic literature.

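### Time-to-revascularisation has no single status and no time horizon, yet log-rank-optimised cut-points are planned on what are likely to be few events

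*Protocol article*

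**What the plan says.** Three places in the protocol article bear on this outcome.

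- **Secondary and exploratory outcomes.** The secondary list covers treadmill distances and their change, chair stand, handgrip, 2-minute walk and the walking questionnaire. Time-to-revascularisation is absent. Revascularisation after the primary endpoint appears under "Exploratory outcomes assessed at 6, 12, and 18 months—such as late revascularization, MALE, MACE, and all-cause mortality". The reason for restraint is given: "Given the anticipated low event counts during extended follow-up in this cohort", "exploratory outcomes will be reported descriptively and interpreted as hypothesis-generating only".
- **Table 3, row 5, and the component-analysis paragraph of Statistical analysis.** The revascularisation-free survival component has this rationale: "Isolates the predictive relationship with intervention requirement. Mandatory pre-specified secondary analysis; reported in all primary publications regardless of composite outcome result". It is a component of the 3-month composite.
- **Threshold paragraph of Statistical analysis.** "For the secondary time-to-revascularization outcome, optimal cut-points will also be identified by maximizing the log-rank statistic via survminer::surv_cutpoint". No horizon is given. The muscle-density threshold is single; for VAT area the derivation has "men and women analyzed independently to account for dimorphic adipose tissue distribution". The reporting rule is "Each threshold derivation will report the optimal cut-point value, Youden index, sensitivity, specificity, and 95% bootstrap CI". The same paragraph says that "internal optimism is anticipated and explicitly acknowledged".

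**The concern.** A reader cannot tell whether the secondary time-to-event outcome is the 3-month component or revascularisation through 18 months. If it is the former, almost no events may be available. If it is the latter, the protocol has already said that events will be too few for more than description, and a data-driven threshold search goes beyond description.

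At stake is the usefulness of the thresholds. They are meant to complement the Youden cut-points and to be carried into external validation. A cut-point chosen on a handful of events, split further by sex for VAT, is mostly a product of chance. The reporting rule also does not fit: Youden index, sensitivity and specificity need a binary outcome, and they are not directly defined for a log-rank cut on censored times unless a fixed time point and a method for censoring are added.

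**Working it through.** **The plan's own figure.** Sample size: 100/(1 − 0.22) = 128.2, stated as 128; 128 × 0.78 = 99.8 evaluable; 100 × 0.40 = 40 failures. This reproduces. The 40% merges non-completion with early revascularisation, so no revascularisation count can be read from it.

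**Expected revascularisations.** The only rate in the document is 25% over five years, from another trial's conservative arm (Introduction). With a constant hazard (an assumption), risk by month m is 1 − 0.75^(m/60).

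- 3 months: 1 − 0.75^(3/60) = 0.0143; × 128 = 1.8 events (1.4 of 100).
- 18 months: 1 − 0.75^(18/60) = 0.0827; × 128 = 10.6 events (8.3 of 100).
- Women by 18 months, of 128: 10.6 × 0.30 = 3.2. The share of women is assumed; 25% gives 2.6 and 40% gives 4.2.
- Upper bound, all 25% occurring within 18 months: 128 × 0.25 = 32.

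**Stability of the selected cut-point.** Cohorts of 128 were simulated with a true step (hazard ratio 2 below the 40th percentile of the predictor), follow-up to 18 months, and the cut chosen by maximal log-rank statistic over the central 80% of values. The trimming is an assumption.

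- About 10.6 events: 95% of selected cuts lie between roughly the 10th and 88th percentiles, nearly the whole search interval.
- About 32 events: roughly the 10th to 87th. More of the selections fall near the true step, but the tails barely shrink.

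**A p-value at that cut, if someone quoted one.** Null data, 4,000 data sets per setting, unadjusted two-sided log-rank test at 0.05 at the selected cut, with 10% or 20% trimmed from each end:

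| Patients, events | 10% trimmed | 20% trimmed |
|---|---|---|
| 128, 2 | 24% | 24% |
| 128, 10 | 38% | 29% |
| 128, 11 | 41% | 31% |
| 128, 32 | 42% | 32% |
| 90 men, 7 | 34% | 28% |
| 30–38 women, 3 | 27–30% | 24–30% |

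Most settings give about 25–42%. The lowest simulated value was 22% (38 women, 4 events, 20% trimmed).

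**The case against.** The case for leaving the text alone has real substance.

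- **No test is planned.** A reader might infer that the study would present a falsely significant split more than a third of the time. The documents do not support that. The list of reported quantities contains no p-value, and the share falls to about 27–31% in women with three events or in the whole cohort at 10 to 11 events with heavier trimming.
- **The event counts are not the protocol's.** A reader might take about 10 events as its own forecast. The rate belongs to another trial, which the Sample size section says was not designed to quantify SET-specific non-response. This cohort is selected for prior revascularisation work-up, so its rate may differ in level and timing.
- **The conflict is not absolute.** A reader might infer that the sections flatly contradict each other. The word secondary may refer to the mandatory component in Table 3, and a hypothesis-generating label is compatible with an exploratory cut-point.
- **Safeguards exist.** Statistical analysis calls all classification thresholds exploratory, keeps them out of the primary model, nests cut-point derivation in its own bootstrap loop, and requires external validation.

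All of this stands and limits the severity. It does not settle the outcome's status or horizon. Reading it as the 3-month component leaves about 2 events on the borrowed rate. A bootstrap interval can reveal instability but cannot make a threshold usable. The labels themselves are mixed: thresholds are post hoc and exploratory in the analytical hierarchy, but prespecified study outcomes in the threshold paragraph.

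**Conclusion.** The point holds as an inconsistency of status, an undefined horizon and a poorly chosen threshold method. The absence from the secondary list, the missing horizon and the ill-fitting reporting rule rest on the text alone. The size rests on assumptions: a borrowed 25% over five years, a constant hazard, an assumed 30% women, and trimmed tails in the search. Across the range of about 2 events (3 months), 10.6 (18 months) and at most 32, no count gives a dependable cut-point; even a true hazard ratio of 2 leaves it spread over roughly the 10th to 88th percentile at 10.6 events. A nominal p-value quoted there without adjustment would mislead in about 25–42% of null cohorts, but none is planned.

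A reader might also infer that the main result is compromised. It is not: H1 and H2 are tested on continuous z-scores in a logistic model that uses no threshold. Severity is minor to moderate.

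**What to change.** Give time-to-revascularisation one status and one horizon, worded alike in Table 3 row 5, Secondary and exploratory outcomes, and both the component-analysis and threshold paragraphs of Statistical analysis. Changing only one of these would leave a new mismatch with the mandatory revascularisation-free survival analysis.

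Delete the sentence on log-rank-maximised cut-points. Report cumulative incidence descriptively. If an association is wanted, give one estimate per SD of the continuous z-score with its confidence interval, in line with the protocol's own principle that inference rests on continuous predictors.

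Deletion is not the only option. If a log-rank cut-point is kept, label it exploratory, require a minimum number of events (per sex for VAT), report no p-value unless it is adjusted for maximal selection, and replace the Youden index, sensitivity and specificity with quantities defined for censored data.

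The cost is one sentence removed and a definition added before enrolment, planned for June 2026. The downside is that no time-to-event threshold would be reported.

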### Additional measurements

The Clinical Frailty Scale (CFS) and Short Physical Performance Battery (SPPB) will be administered at T0 and T1 as auxiliary variables for multiple imputation and as potential confounders in robustness analyses; they are not considered primary predictors. A fasting metabolic panel (including fasting glucose, glycated hemoglobin [HbA1c], lipid profile, and high-sensitivity C-reactive protein [hsCRP]) will be obtained at T0 and T1. Serum samples for exploratory biomarker analyses (including adiponectin, leptin, and interleukin-6 [IL-6]) will be stored at --80^∘^C from all study participants at T0 and T1 for batched analysis. Assays will be performed after the first 40 participants complete follow-up (interim descriptive report) and on the full cohort at study closure. No formal stopping rule or Phase 2 decision gate applies; these analyses are exploratory and will be reported as such.

### Data management

Clinical and outcome data are captured and managed within the institutional electronic data management system, utilizing structured data entry forms, automated range validation rules, and comprehensive audit trails. Participant data are pseudonymized at the point of entry; the linkage key is maintained separately by the principal investigator and is accessible only to authorized study personnel. All data handling adheres to applicable national data protection legislation and the General Data Protection Regulation. Weekly completeness reviews are conducted by the designated data manager. Source document verification is performed on a random 10% sample of participant records, targeting an error rate of less than 2%. All outcome assessors complete structured training with a minimum passing threshold of 90% and undergo annual recertification.

## Discussion

The central methodological premise of this study posits that routine diagnostic CTA —already part of standard anatomical assessment for symptomatic PAD patients considered for revascularization—contains quantitative metabolic information that is typically disregarded in clinical practice [2, 15]. By extracting L3 body composition data from existing imaging using an automated neural network, this protocol imposes no additional burden on patients while yielding metabolic predictors with established biological relevance.

It is crucial to explicitly state a critical point regarding the scope of this study. L3 CT body composition measures systemic metabolic reserve—reflecting the whole-body distribution and quality of skeletal muscle and adipose tissue compartments—and does not directly quantify ischemia-specific myopathology in the affected lower limb musculature. The predictive hypothesis is based on two complementary mechanisms: (a) L3 skeletal muscle density reflects systemic mitochondrial function and intramuscular lipid infiltration, which constrain aerobic adaptation capacity independently of localized ischemia; and (b) VAT area quantifies a systemic pro-inflammatory endocrine compartment, whose adverse effects on exercise metabolism are well characterized across cardiovascular populations [14]. These mechanisms operate systemically rather than being limb-specific. Their relationship to PAD-specific outcomes will be delineated and bounded by the derivation cohort data; localized thigh or calf CT may provide complementary information and is pre-specified for future validation studies.

The growing body of evidence supporting L3-based opportunistic phenotyping in cardiovascular populations facilitates methodological translation to this context. Our group has demonstrated that AutoMATiCA-derived L3 parameters independently predict overall survival following TAVI [16] and has developed a user-friendly clinical implementation tool based on the same methodology [17]. The direct parallel with SET —an intervention whose outcome significantly depends on patients’ physiological reserve for aerobic adaptation—provides mechanistic justification for this approach in PAD. The broader context of opportunistic CT phenotyping programs [28, 29] underscores both the scientific precedent and the scalability of zero-burden body composition extraction from routine vascular imaging.

The composite primary endpoint is designed to capture the two clinically relevant failure modes of SET: failure to achieve meaningful functional improvement and progression to revascularization before completing the program. Functional improvement thresholds are anchored to absolute improvement benchmarks for treadmill-based SET documented in the 2019 AHA scientific statement on optimal exercise programs for PAD [19], representing the minimum criteria for a meaningful clinical response. Revascularization events are independently adjudicated and classified to facilitate sub-analyses restricted to guideline-concordant intervention decisions [4], addressing concerns that elective revascularization may be influenced by patient preference rather than objective clinical failure. The Fine–Gray competing risks model is employed for time-to-event analyses to appropriately account for the competing event of death in this elderly and comorbid population [30], thus avoiding biases that could arise from standard Cox regression in the presence of significant competing risks.

The statistical framework is calibrated to the explicit derivation role of this study. With an expected 40 treatment failures, inferential precision for model discrimination will be limited, and all conclusions will therefore be confined to the direction and magnitude of predictor associations [26, 27]. This study lacks the event volume necessary to establish validated, externally generalizable clinical decision thresholds, and any such interpretations would be premature. Bootstrap internal validation will estimate optimism-corrected model performance; however, internal validation cannot substitute for external replication in an independent cohort.

Strengths of this protocol include: a fully guideline-concordant SET program adhering to the AHA 2019 specifications [19]; a composite primary endpoint with minimal clinically important difference-informed thresholds and pre-specified sensitivity analyses; appropriate competing risks methodology; Bonferroni correction for two co-primary hypotheses (H1 and H2); bootstrap internal validation encompassing the entire analytical pipeline, including spline assessment; MICE with pattern-mixture sensitivity analyses for missing data; prospective trial registration; and adherence to Transparent Reporting of a multivariable prediction model for Individual Prognosis Or Diagnosis (TRIPOD) [31] and Strengthening the Reporting of Observational Studies in Epidemiology (STROBE) [32] reporting standards. Furthermore, an opportunistic, zero-burden imaging approach is directly scalable to clinical practice.

Limitations must be stated with equal clarity. This is a single-center derivation cohort; generalizability to other health systems, exercise program models, and patient populations cannot be assumed. The L3 vertebral level does not directly capture ischemia-specific lower limb myopathology, and the biological distance between L3 and the affected musculature is acknowledged as a limitation rather than a design strength. No PAD-specific HU threshold for myosteatosis has been prospectively validated; the cohort-derived threshold established in this study is exploratory and hypothesis-generating (see sensitivity analyses #8 and #9 in Table 3 for assessment of alternative literature-derived values of 33 HU and 41 HU, respectively). AutoMATiCA was validated in oncology and critical care cohorts [20], but not in PAD; vascular calcification—highly prevalent in PAD—represents a specific source of measurement error: calcified plaque within or adjacent to the muscle compartment may not be fully excluded by the 150 HU ceiling, potentially inflating skeletal muscle density estimates; this systematic bias is specific to PAD imaging and is acknowledged as a limitation that cannot be fully quantified without PAD-specific validation data. The performance of the segmentation algorithm in the context of PAD-specific imaging protocols has not been independently established. The three-month primary endpoint may not capture delayed functional divergence between metabolic phenotype groups. The observational design precludes causal inference. The TASC II anatomical disease severity classification is recorded as a baseline variable and is included as a covariate in the expanded confounding model; however, as a potential confounder linking disease anatomical extent to both body composition phenotype and SET response, residual confounding by vascular disease extent cannot be fully excluded in a derivation cohort of this size. Requiring an existing diagnostic CTA introduces a selection bias: patients without prior CTA workup are excluded, meaning the cohort reflects those who have undergone imaging-based revascularization evaluation. Transportability to settings without routine CTA-based PAD workup or to patients managed without imaging evaluation cannot be assumed and necessitates specific consideration in external validation studies.

Future research priorities are as follows. First, multicenter external validation of the predictor model derived here is the immediate next step. Second, a mechanistic comparison of L3 versus thigh and calf CT within the same PAD cohort would clarify the respective contributions of systemic and local body composition phenotyping to outcome prediction. Third, if predictor associations are confirmed through external validation, a randomized controlled trial of metabolic phenotype-guided versus anatomy-guided treatment selection is warranted to determine whether body composition-stratified management improves clinically meaningful outcomes.

## Conclusion

Outcome heterogeneity in SET for intermittent claudication remains a clinically unresolved challenge: a substantial proportion of patients either do not complete the SET program or fail to achieve meaningful functional benefit or require revascularization within three months, yet no validated pre-therapy metabolic predictor exists to identify these individuals. This prospective observational study aims to test the hypothesis that L3 CT-derived skeletal muscle density and VAT area—extracted opportunistically from routine diagnostic CTA at zero additional patient burden at baseline—will independently predict three-month SET outcomes in Fontaine IIa–IIb claudicants. If the findings from the derivation cohort support the primary hypotheses, and if those findings are subsequently confirmed in external multicenter validation, metabolic phenotype-guided patient selection could enhance treatment efficiency, reduce avoidable rehabilitation failure, and facilitate more rational integration of SET and revascularization pathways. This protocol constitutes the derivation phase; external validation is the essential next step before clinical translation. All thresholds, phenotype categories, and discrimination estimates reported from this study are derived from the cohort findings. Clinical translation requires prospective testing in an independent external multicenter cohort before any application to patient selection or treatment stratification. The findings of this study should not be generalized to clinical practice or patient populations that differ substantially from this single-center Czech cohort without formal external validation.

**Dissemination:** The results of this study will be submitted for publication in a peer-reviewed journal and presented at relevant national and international scientific conferences; no publication restrictions have been imposed by the funders.

